### Statistical Methods for Analyzing Efficacy Outcomes

#### Primary Outcomes

The primary outcome analysis will use a mixed-effect model repeated measure (MMRM) approach, including each treatment group and visit time point as fixed factors, with participants as random factors, and accounting for interactions between groups and visit time points. Variables that show statistically significant differences in demographic or sociological characteristics, or other factors potentially influencing anxiety disorders, will be incorporated as fixed factors. Results will be presented with means, 97.5% CIs, and *P* values. In addition, if significant baseline differences exist between groups, an Analysis of Covariance (ANCOVA), adjusted for baseline values as a covariate, will be conducted.

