**Secondary Outcomes**
The secondary outcomes will be assessed as follows:Changes in HAM-A scores from baseline to week 8 between the EA-MNS group and the EA-VNS group.Evaluation of rates of loss of diagnosis and complete remission of anxiety disorder, as measured by HAM-A scores, from baseline to week 8 between the EA-MNS group and the Usual Care group.Evaluation of rates of loss of diagnosis and complete remission of anxiety disorder, as measured by HAM-A scores, from baseline to week 8 between the EA-VNS group and the Usual Care group.Evaluation of rates of loss of diagnosis and complete remission of anxiety disorder, as measured by HAM-A scores, from baseline to week 8 between the EA-MNS group and the EA-VNS group.Changes in Beck Anxiety Inventory (BAI), Beck Depression Inventory-II (BDI-II), Patient Health Questionnaire-15 (PHQ-15), World Health Organization Quality of Life Assessment Instrument abbreviated version (WHOQOL-BREF), Penn State Worry Questionnaire (PSWQ), Panic Disorder Severity Scale (PDSS), and Leibowitz Social Anxiety Scale-Self Report (LSAS-SR) scores from baseline to week 8 between the EA-MNS group and the Usual Care group.Changes in BAI, BDI-II, PHQ-15, WHOQOL-BREF, PSWQ, PDSS, and LSAS-SR scores from baseline to week 8 between the EA-VNS group and the Usual Care group.Changes in BAI, BDI-II, PHQ-15, WHOQOL-BREF, PSWQ, PDSS, and LSAS-SR scores from baseline to week 8 between the EA-MNS group and the EA-VNS group.

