#### Secondary Outcomes

The analysis of secondary outcome variables will adhere to the same methodology used for the primary outcomes. Changes in continuous variables from baseline to week 8 in BDI-II, BAI, PHQ-15, WHOQOL-BREF, PSWQ, PDSS, and LSAS-SR will be assessed using the same analytical approach, with a significance level set at 5%. To evaluate the differences in measurements before and after the intervention within each group, the Student Paired *t* test or Wilcoxon signed rank test will be used for both primary and secondary outcomes. Additionally, to examine the trend changes over time between the EA-MNS and EA-VNS groups, Repeated Measures ANOVA will be conducted. This analysis will include testing the interaction between the groups and visits to ascertain how differences evolve over time. If the interaction is found to be significant, post hoc tests will be implemented to identify significant differences between the groups at specific time points based on baseline measurements. Furthermore, the binary variables such as loss of diagnosis and complete remission of anxiety disorder, as assessed by HAM-A, will be compared between groups using logistic regression, which will provide odds ratios and 95% CI.

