### Statistical Methods to Handle Missing Data

When using the MMRM for variable analysis, no separate imputation for missing values will be conducted. Conversely, in cases where ANCOVA is used, missing values will be imputed using the Multiple Imputation method.

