## Results

This study was funded in December 2022. The first participant was enrolled on December 15, 2022, and the final participant completed the intervention on November 22, 2024. A total of 60 participants were enrolled, and 51 participants completed the intervention. Data collection was conducted from December 13, 2022, to November 22, 2024. Data analysis is currently underway, and the results are expected to be published in 2025. The CONSORT (Consolidated Standards of Reporting Trials) flowchart depicting the study process is presented in Figure 4.

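### If the participant random factor is the primary MMRM's only source of within-participant correlation, the week-8 HAM-A standard error can be wrong in either direction; the added repeated-measures ANOVA duplicates that model with weaker missing-data handling

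*Protocol article*

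**What the plan says.** Under Primary Outcomes in the statistical methods, the article specifies an MMRM "including each treatment group and visit time point as fixed factors, with participants as random factors", with a group-by-visit interaction. It names no covariance structure. The primary tests are two-sided at 2.5%, with 97.5% confidence intervals.

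Under Secondary Outcomes in the statistical methods: "The analysis of secondary outcome variables will adhere to the same methodology used for the primary outcomes". The secondary outcomes listed under Efficacy Variables include "Changes in HAM-A scores from baseline to week 8 between the EA-MNS group and the EA-VNS group", so the MMRM already covers that comparison. The article then adds: "Additionally, to examine the trend changes over time between the EA-MNS and EA-VNS groups, Repeated Measures ANOVA will be conducted". This ANOVA includes a group-by-visit interaction test and, if that is significant, post hoc tests at specific time points.

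On missing values, the article says: "When using the MMRM for variable analysis, no separate imputation for missing values will be conducted". ANCOVA gets multiple imputation. The repeated-measures ANOVA is not mentioned. The Full Analysis Set (FAS), on which all efficacy data are to be analysed, admits anyone with a baseline value and one later primary-outcome value.

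**The concern.** There are two separate issues.

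**Covariance in the primary model.** A random participant intercept with independent residuals implies compound symmetry: one variance for all visits and one correlation for all pairs of visits. Every visit-to-visit contrast then shares one pooled error term. The primary contrast spans baseline to week 8, the longest gap. If the correlation is lower over that gap, or the variance grows after baseline, the pooled term is too small for this contrast and the 2.5% level is exceeded. If the pattern is reversed, the term is too large and power is lost.

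**A second analysis of the EA-MNS versus EA-VNS trend.** In its classical form, repeated-measures ANOVA assumes sphericity and drops any participant with a missing visit. A participant seen at week 4 but not at week 8 belongs to the FAS and contributes to the MMRM, but would be lost from the ANOVA. The same question could then get two answers from different sets of participants.

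**Working it through.** **Inputs from the article.** There are 20 participants per arm in three arms. HAM-A is measured at baseline, week 4 and week 8. The primary alpha is 2.5% two-sided and the secondary alpha is 5%. "A total of 60 participants were enrolled, and 51 participants completed the intervention", so 60 − 51 = 9 did not (15%).

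**Inputs assumed.** The article gives no HAM-A SDs or between-visit correlations, so a range is used: SD 7 throughout, or rising 6/7/8 or 5/7/9, with correlations from 0.3 to 0.7. Data are normal, and the covariance is the same in every arm. The article has no figure of its own on this point to reproduce.

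**Standard error of the week-8 change, baseline in the response.** V0 and V8 are the variances at baseline and week 8, and C08 is their covariance.

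- True per-participant variance of change: V0 + V8 − 2·C08.
- Variance under compound symmetry: 2 × (mean of the three variances − mean of the three covariances).
- SE ratio: square root of (compound-symmetry variance ÷ true variance).

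Example with SD 7 and correlations (0–4, 0–8, 4–8) of 0.70/0.40/0.70:

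- The true variance is 98 × (1 − 0.40) = 58.8.
- The mean correlation is 0.60, so the compound-symmetry variance is 98 × (1 − 0.60) = 39.2.
- The ratio is √(39.2/58.8) = 0.82.

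**If change scores at weeks 4 and 8 are the response.** There is then one correlation, and only equal variance is imposed. The pooled variance is the mean of the two change variances. In the same example, the week-4 change variance is 98 × 0.30 = 29.4, the mean is (29.4 + 58.8)/2 = 44.1, and the ratio is √(44.1/58.8) = 0.87.

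Type I error with baseline in the response comes from 20,000 simulated trials per scenario (20 per arm, 114 residual df). For change scores it is the normal approximation 2Φ(−2.241 × ratio), where 2.241 is the two-sided 2.5% critical value.

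| SDs | Correlations 0–4 / 0–8 / 4–8 | SE ratio, baseline in response | Type I error | SE ratio, change scores | Type I error |
|---|---|---|---|---|---|
| 7/7/7 | 0.50/0.50/0.50 | 1.00 | 2.6% | 1.00 | 2.5% |
| 7/7/7 | 0.60/0.45/0.60 | 0.91 | 4.3% | 0.93 | 3.7% |
| 7/7/7 | 0.70/0.40/0.70 | 0.82 | 6.4% | 0.87 | 5.2% |
| 6/7/8 | 0.60/0.35/0.60 | 0.86 | 5.3% | 0.87 | 5.1% |
| 5/7/9 | 0.60/0.30/0.70 | 0.80 | 7.1% | 0.84 | 6.0% |
| 7/7/7 | 0.40/0.60/0.40 | 1.15 | 1.1% | 1.12 | 1.2% |

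A test using the change score's own variance, which an unstructured model reproduces in complete data, gave 2.4% to 2.6% in every row. With 17 per arm the results were similar.

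**Scales with only baseline and week 8.** The compound-symmetry variance is 2 × [(V0 + V8)/2 − C08] = V0 + V8 − 2·C08, which is the true value. The problem is therefore confined to HAM-A and BAI.

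**Repeated-measures ANOVA, two electroacupuncture arms.** In the same scenarios the uncorrected interaction test rejected in 4.8% to 6.4% of trials at nominal 5% (20 per arm), and in 5.1% to 6.6% with 17 per arm. The sphericity failure alone does little harm.

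Case deletion can matter more. It was checked with 15% dropout per arm, SD 7, correlations 0.60/0.45/0.60 and no true difference between arms:

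| Dropout pattern | Complete-case bias (HAM-A points) | Likelihood bias |
|---|---|---|
| Completely at random | −0.02 | −0.02 |
| Depends on week-4 change, same in both arms | −0.06 | −0.06 |
| Worse responders leave one arm only | −0.77 | −0.02 |
| Opposite patterns in the two arms | −1.47 | 0.05 |

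**The case against.** The strongest reply is that the article never states a compound-symmetry structure. MMRM usually means a modelled within-participant covariance, and the random-factor phrase may be loose shorthand for clustering by participant. A condensed article commonly leaves covariance structure and degrees of freedom to the analysis plan. This stands to the extent that silence on the covariance is not itself a finding, and constant correlation is the literal reading rather than an explicit statement. But the article does say how participants enter the model. Followed as written, that is a random intercept, and an unstructured MMRM needs no such term.

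The size also rests on assumed inputs, the direction can reverse, and modelling change scores shrinks the effect. All of that is correct.

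Several stronger readings are tempting but unsupported:

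- **The mixed model drops incomplete cases.** It does not. A likelihood model keeps every observed visit, and case deletion concerns only the ANOVA.
- **The EA-MNS versus EA-VNS result depends on the ANOVA.** It does not. The week-8 comparison belongs to the MMRM, and the ANOVA is introduced as an additional look at trend.
- **The ANOVA would lose 9 of 60 participants.** The 9 span all three arms, whereas the ANOVA covers two arms planned at 40. Not completing the intervention is also not the same as a missing HAM-A score.
- **The within-group paired tests are a misuse.** The article offers them as before-and-after comparisons, not as treatment effects. Whether to print their p values is a reporting preference.

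**Conclusion.** The point holds in a conditional form. If the participant random factor is the only source of within-participant correlation, the week-8 HAM-A standard error can be about 0.80 to 1.15 times its true value. The type I error is then about 1% to 7% at nominal 2.5%, or about 1% to 6% with change scores as the response. These ranges depend entirely on the assumed SDs and correlations. They show that the stated model is not protected, not that the trial's primary tests are inflated. BAI is exposed in the same way; the two-visit scales are not.

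The repeated-measures ANOVA is redundant next to the MMRM group-by-visit contrasts. In its classical form it conflicts with the FAS definition, and the missing-data section has no rule for it. Its interaction test is only mildly inflated. Its complete-case bias is near zero unless dropout patterns differ between the two arms. The number it would lose cannot be read from the text.

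**What to change.** Replace the participant random factor with an unstructured within-participant covariance over visits and Kenward-Roger degrees of freedom. State whether baseline is part of the response. Take all three week-8 contrasts and the EA-MNS versus EA-VNS trend from this one model, and delete the separate repeated-measures ANOVA with its conditional post hoc tests. If the analysis plan already specifies an unstructured covariance, only the article's wording and the ANOVA need attention.

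The cost is small. Three visits need 3 × 4 / 2 = 6 covariance parameters instead of 2, which is estimable with 60 participants. In complete data the error df for the contrast falls from 114 to 57, which moves the two-sided 2.5% critical value from 2.27 to 2.30. Intervals may be wider where compound symmetry would have understated the error, and narrower where it would have overstated it. The Results section says analysis is underway, so the change should be dated, with a statement of whether comparative results had been seen.

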**Primary Outcome**
The primary outcome will be assessed by analyzing changes in the Hamilton Anxiety Rating Scale (HAM-A) scores from baseline to week 8 in two separate comparisons:Between the electroacupuncture-median nerve stimulation (EA-MNS) group and the Usual Care group.Between the electroacupuncture-vagus nerve stimulation (EA-VNS) group and the Usual Care group.Research HypothesisHypothesis 1 [H0 : μ1 = μ2, H1 : μ1 ≠ μ2]μ1: Changes in HAM-A score from baseline to week 8 in the EA-MNS groupμ2: Changes in HAM-A score from baseline to week 8 in the Usual Care groupHypothesis 2 [H0 : μ3 = μ2, H1 : μ3 ≠ μ2]μ2: Changes in HAM-A score from baseline to week 8 in the Usual Care groupμ3: Changes in HAM-A score from baseline to week 8 in the EA-VNS group

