### Statistical Methods: Definition of the Analysis Set

The analysis sets for evaluating data obtained in this clinical trial are defined as follows: the Full Analysis Set is in accordance with to the intent-to-treat principle, encompassing all participants who met the inclusion and exclusion criteria, were randomly assigned, and for whom baseline measurements and at least 1 postbaseline primary outcome was obtained. The Per Protocol Set (PPS) includes participants from the FAS who have adhered to at least 75% of the total intervention and do not meet any discontinuation or dropout criteria. The Safety Analysis Set (SAS) comprises all participants who have undergone at least one safety assessment following random assignment.

All data, including efficacy outcomes, will be analyzed using the FAS, with the PPS serving as a secondary analysis group for additional analyses. Safety variables will be analyzed using SAS. Continuous data will be presented as means and confidence intervals, while categorical data will be presented as frequencies and percentages (%). If necessary, initial characteristics of participants measured at screening or baseline may be categorized for subgroup analysis.

Unless specifically stated otherwise, all statistical analyses in this study's results will be conducted as 2-sided tests, with a significance level set at 5%. However, for the analysis of the primary outcome, the significance level will be set at 2.5%. Statistical analyses will be performed using SAS software (version 9.4 or higher, SAS Institute).

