### Statistical Analysis of Demographic and Baseline Characteristics

In this study, descriptive statistics for demographic and pretreatment characteristics will be presented for each group. Continuous variables will be analyzed using either ANOVA or the Kruskal-Wallis test, depending on the data distribution. Categorical variables will be analyzed using the chi-square test or Fisher exact test; Fisher exact test will be applied when more than 25% of cells in a contingency table have an expected frequency of less than 5. If necessary, significant differences in baseline characteristics between groups will be adjusted for by incorporating these characteristics as covariates in the efficacy variable analysis.

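### The primary mixed model leaves out baseline HAM-A, and baseline significance tests decide what is adjusted for: precision is lost and the covariate set depends on the data

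*Protocol article*

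**What the plan says.** All references are to the Protocol article.

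- **Endpoint** (Efficacy Variables, Primary Outcome): "changes in the Hamilton Anxiety Rating Scale (HAM-A) scores from baseline to week 8 in two separate comparisons", each electroacupuncture arm against usual care.
- **Primary model** (Statistical Methods for Analyzing Efficacy Outcomes, Primary Outcomes): an MMRM "including each treatment group and visit time point as fixed factors, with participants as random factors", plus the group-by-visit interaction. Baseline HAM-A is not among the terms.
- **Other covariates in that model** (same section): "Variables that show statistically significant differences in demographic or sociological characteristics, or other factors potentially influencing anxiety disorders, will be incorporated as fixed factors". The section on demographic and baseline characteristics repeats the rule, with a qualifier that it applies where needed: "significant differences in baseline characteristics between groups will be adjusted for by incorporating these characteristics as covariates in the efficacy variable analysis".
- **Baseline HAM-A** (Primary Outcomes): "if significant baseline differences exist between groups, an Analysis of Covariance (ANCOVA), adjusted for baseline values as a covariate, will be conducted". The sentence presents the ANCOVA as an addition and does not say which result decides.
- **Baseline test** (demographic and baseline section): "Continuous variables will be analyzed using either ANOVA or the Kruskal-Wallis test, depending on the data distribution".
- **Levels** (Definition of the Analysis Set): tests in general "will be conducted as 2-sided tests, with a significance level set at 5" per cent, but "for the analysis of the primary outcome, the significance level will be set at 2.5" per cent.
- **Missing data**: no imputation under the MMRM, multiple imputation under the ANCOVA.

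The secondary outcomes follow the same methodology.

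**The concern.** In a randomised comparison, a significant baseline difference is a chance event. Testing for one says nothing about whether the variable predicts outcome. The rule can pass over a strong predictor that is mildly imbalanced and admit an irrelevant one that happens to differ. Baseline HAM-A is an obvious candidate predictor of the week-8 score, and it is already collected.

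Two things are at stake. The first is precision: the sample is fixed at 20 per arm without a power calculation, and data collection is over, so only the analysis can still improve it. The second is prespecification: the covariates in the primary MMRM cannot be known until the arms have been compared at baseline. The article also leaves open how the MMRM and the ANCOVA rank, although they handle missing data differently.

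**Working it through.** **The plan's own figures.** Sample size: 3 × 15 = 45, raised to 3 × 20 = 60. No power, SD or effect size is stated, so there is no power figure to reproduce. Primary level: 5% / 2 = 2.5% for each of two comparisons, which agrees with the text.

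**Inputs from the article.** Three arms of 20, 1:1:1; two-sided 2.5% for the primary comparisons; two-sided 5% for the baseline test (the general default, since no other level is given).

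**Assumptions, not in the article.** A true effect of 0.8 SD of the HAM-A score; a baseline to week-8 correlation r from 0.3 to 0.8; equal SD at both times; complete data.

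**Step 1: does the listed MMRM adjust for baseline implicitly?** No. Fitted to complete simulated data, its week-8 contrast equalled the simple difference in mean change to rounding error, whether baseline was entered as a visit or subtracted from the score.

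**Step 2: how often does the baseline HAM-A test fire?** By construction in about 5% of randomisations (simulated 4.9-5.1%). Baseline adjustment by that route is therefore absent in about 95%.

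**Step 3: what does omission cost?** In units of SD², the residual variance is 2(1 − r) for a change score and 1 − r² with baseline as a covariate. The ratio is (1 − r²) / [2(1 − r)] = (1 + r)/2. The unadjusted sample size giving the same precision as 20 per arm adjusted is 20 / [(1 + r)/2]. Power comes from simulated trials with 3 × 20 participants. The unadjusted column lets ANCOVA take over when the baseline test fires; never adjusting gives almost the same (44%, 59% and 83% at r = 0.3, 0.5 and 0.7).

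| r | Variance ratio | Equivalent n per arm | Power, no routine adjustment | Power, baseline always in |
|---|---|---|---|---|
| 0.3 | 0.65 | 30.8 | 45% | 63% |
| 0.4 | 0.70 | 28.6 | 52% | 67% |
| 0.5 | 0.75 | 26.7 | 60% | 72% |
| 0.6 | 0.80 | 25.0 | 71% | 79% |
| 0.7 | 0.85 | 23.5 | 83% | 88% |
| 0.8 | 0.90 | 22.2 | 95% | 97% |

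The article reports 51 of 60 completing the intervention. If these were spread evenly (51 / 3 = 17 per arm), the figures would be 38% against 55% at r = 0.3, 52% against 64% at 0.5, and 76% against 82% at 0.7.

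**Step 4: type I error.** With no true effect, letting the baseline HAM-A test decide between change score and ANCOVA rejects in about 2.1-2.4% of trials, against the nominal 2.5%.

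**Step 5: the other covariates.** The 5% in step 2 belongs to one test. With k independent baseline tests at 5%, the chance that at least one covariate enters by luck is 1 − 0.95^k: 23% for k = 5, 40% for k = 10, 54% for k = 15. The article does not give k, and real baseline variables are correlated, so these figures only illustrate the point.

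**The case against.** **The article names one primary analysis.** It is the MMRM, and the ANCOVA is introduced as something extra. The separate missing-data rules also fit two analyses that coexist. A reader might infer that the baseline test chooses the primary model, but the text does not establish that, and the supplementary reading is more natural. This stands, yet it does not rescue precision: on that reading the primary result is never baseline-adjusted by that route. The other covariates in the MMRM remain data-driven.

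**False positives.** A reader might infer an inflated error rate, because among the roughly 16% of trials with a pairwise baseline imbalance of 0.4-0.7 SD that does not trigger the rule, the unadjusted contrast rejects in about 4-5% at r = 0.4-0.6. That figure is conditional on a selected imbalance. In untriggered trials with imbalance below 0.4 SD, the rate is 1.3-1.7%. Over all randomisations the contrast is unbiased and the error rate is slightly below nominal, so the stronger reading fails.

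**The size of the loss rests on assumed inputs.** This stands. The article justifies its sample size by feasibility and exploratory analysis and claims no power, so no stated figure is broken.

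**The covariate rule may be looser than a pure significance filter.** The clause on other factors that may influence anxiety disorders can be read as exempt from the test. That ambiguity stands, but an open-ended list is not prespecification either.

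**This could be left to the analysis plan.** Finer model detail could be. But the article states a selection rule, and the rule itself is the problem.

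**Conclusion.** The concern holds as a matter of precision and prespecification. The listed primary MMRM omits baseline HAM-A, the only stated baseline adjustment depends on a test that fires in about 5% of randomisations, and other covariates are selected by baseline significance tests. Overall type I error is not at risk from the baseline HAM-A rule, and the planned unadjusted contrast is valid.

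Under an assumed 0.8 SD effect with 20 per arm, the power gain from routine adjustment falls from about 18 percentage points at r = 0.3 (63 − 45) to 12 at r = 0.5 (72 − 60) and 2 at r = 0.8 (97 − 95). The direction does not depend on where r lies within that range; the size does. The 5% firing rate should not be applied to the other covariates jointly. The ANCOVA's role is unresolved in the text, and both readings leave baseline HAM-A out of the primary result in most or all cases.

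**What to change.** 1. Specify one primary MMRM for HAM-A at weeks 4 and 8 with group, visit, group-by-visit, baseline HAM-A and baseline-by-visit always included. Name the week-8 contrast of each electroacupuncture arm against usual care as the deciding estimate.
2. Delete covariate selection by baseline significance tests, in both the primary-outcome section and the baseline-characteristics section. Any further covariate should be named in advance.
3. Drop the conditional ANCOVA, or keep it as a labelled sensitivity analysis.
4. For scales measured only at baseline and week 8, always include the baseline score.

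The Results section says data collection has ended and analysis is underway. The change should therefore be made before any unblinded output, or reported as a dated change with the blinding status at that date. The cost is one or two degrees of freedom and that documentation; no new data are needed.
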